**Figure 1 F1:**
[figure not shown]
Summary of enrolment, intervention and assessment procedures based on the SPIRIT figure.

**Figure 2 F2:**
[figure not shown]
Logic model of intervention.

### Sample Size Estimation

The National Institute for Health Research guidelines indicated that no formal power calculation is required for feasibility study (46). As this study will be a feasibility study, a formal power calculation based on identifying evidence for effectiveness will not be performed and no sample size calculation will be undertaken. The sample size of six schools (four intervention and two control arms) will be grouped based on the minimum recommended for a pilot cluster randomized trial (47).

Based on recent experience in local secondary schools, we predict that between 75 and 80 students from each school will reach the age of 15. Therefore, we assume that the sample size will range between 450 and 480 adolescents. This is a pragmatically chosen sample to detect the feasibility evidence, recruitment rates, and any barriers to implement the research methodology. Feasibility study is conducted to determine the necessary sample size needed to evaluate the intervention. It is premature to specify the required sample size for a future trial, however it is useful to get a broad indication of the estimated sample size for the trial. Thus, the sample size for this study will be chosen to provide a sufficient number of schools and students to test each of the three conditions in urban and rural areas and provide an indication of the likely sample size for a full trial.

### Recruitment and Randomisation Procedures

The sample will consist of six schools in Selangor and Perak states in Malaysia as the rural and urban areas, respectively. The sample of six schools will be randomly selected from a list of secondary schools that had previously participated in the MyHeARTs cohort study (48). The previous cohort study followed a stratified sampling design. First, a complete list of the public secondary schools in the selected regions was obtained from the Ministry of Education (MOE) in Malaysia and used as the sampling frame. The schools were classified as urban and rural-based on the criteria provided by the Department of Statistics Malaysia. A total of 15 schools from a cohort that was consisted of eight urban and seven rural schools was chosen as the study sampling frame (48).

The six schools in this study will be first randomly selected from 15 schools, and then the schools will be randomly allocated to the intervention 1, 2, and control arms (two schools per arm). Two schools will be allocated to the intervention 1 group and will receive training only, while two other schools will receive training and subsidies on healthy foods. Another two schools will make up the control group without any involvement in the interventions. However, the control groups will receive manual on healthy canteen at the end of the study. The random selection and allocation of the six schools from the urban and rural locations and division to intervention and control arms will be performed (computer-generated allocation) by an independent statistician from the University of Bristol who will be blind to the school identity. The primary sampling units will be six schools and the secondary sampling will include all 15 years old students of six selected schools who will be invited.

Participants will be recruited from six government-funded secondary schools located in the Selangor (urban) and Perak (rural) areas in Malaysia (three schools from each area). Eligible participants will be Malaysian adolescents (15 years of age) from “secondary three class” (known as “Form three”). The students and their parents or guardians will receive written information about the study as well as consent form 1 week before conducting the intervention and then will be requested to submit the completed consent form next day if possible. The participants will have to speak and write the national language (Malay). Students from religious and vernacular schools will be excluded from the sample since most of them tend to be from a mono-ethnic group.

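### Allocation of the six schools is described with no restriction by urban/rural setting, although each condition is to be tested in both; if it is unstratified, only 40% of allocations achieve this, and the Selangor/Perak labels contradict each other

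*Protocol article*

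**What the plan says.** All of the relevant text is in the Methods of the Protocol article.

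- **Purpose of the sample** (Sample Size Estimation): the sample is chosen to "provide a sufficient number of schools and students to test each of the three conditions in urban and rural areas".
- **Sampling frame** (Recruitment and Randomisation Procedures): the 15 cohort schools "consisted of eight urban and seven rural schools".
- **Selection** (same section): "The six schools in this study will be first randomly selected from 15 schools". That sentence names no strata, but a later paragraph of the section fixes the split, with schools "located in the Selangor (urban) and Perak (rural) areas in Malaysia (three schools from each area").
- **Allocation** (same section): "the schools will be randomly allocated to the intervention 1, 2, and control arms (two schools per arm"). An independent statistician, blind to school identity, generates the allocation by computer. The one sentence linking this step to setting begins "The random selection and allocation of the six schools from the urban and rural locations".
- **Setting labels** (same section): the opening sentence has "six schools in Selangor and Perak states in Malaysia as the rural and urban areas, respectively", so Selangor is rural and Perak urban. The paragraph on participants has "six government-funded secondary schools located in the Selangor (urban) and Perak (rural) areas in Malaysia", the reverse.

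In this section, stratification is mentioned only for the sampling design of the earlier cohort.

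**The concern.** With two schools per arm, a condition is tried in both settings only if its arm holds one urban and one rural school. The allocation as described does not require that. A statistician who applied the text literally could produce an arm with no rural school and another with no urban school, and would still have followed it.

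Setting is not a neutral label here. The Introduction reports that rural students consumed more sugar, cholesterol and energy than urban students. Intervention Development reports that affordability was a major problem for adolescents in rural schools, and the subsidy that separates Intervention 2 from Intervention 1 acts on affordability. Planned Analysis says that effects will be judged by effect size, and Discussion and Conclusion says that the study will inform which of the two interventions goes to a full trial. If the arms being compared differ in setting, those readings mix intervention with setting, and with state as well, because the article ties setting to state.

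The reversed labels add a second problem: from the article alone, a reader cannot tell which three schools form the urban stratum.

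**Working it through.** **Inputs.** Three arms with two schools each, three urban and three rural schools, and a frame of eight urban and seven rural schools, all from Recruitment and Randomisation Procedures. Sample Size Estimation gives 75 to 80 students per school.

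**The plan's own figure.** The article gives no probability of urban/rural balance. Its only related figure is the expected number of students, which reproduces: 6 × 75 = 450 and 6 × 80 = 480.

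**Step 1: all allocations.** If two schools per arm is the only restriction, the number of equally likely allocations is 6!/(2! × 2! × 2!) = 720/8 = 90.

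**Step 2: allocations that meet the aim.** Each arm must receive one urban and one rural school. The urban schools can be assigned in 3! ways and the rural schools in 3! ways: 6 × 6 = 36. The probability is 36/90 = 40%.

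**Step 3: the remainder.** If one arm has two urban schools, the third urban school sits in another arm with a rural school, and the last arm has two rural schools. So every unbalanced allocation has one all-urban, one all-rural and one mixed arm. The three roles can be assigned to arms in 3! = 6 ways. There are C(3,2) = 3 choices of the urban pair and 3 of the rural pair: 6 × 3 × 3 = 54, and 54/90 = 60%. As a check, 36 + 54 = 90. A full enumeration gave the same counts.

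**Step 4: a given pair of arms.** For Intervention 2 and control to be the two single-setting arms, there are 2 ways to assign the roles and 9 choices of schools: 18/90 = 20%. By symmetry, the figure is also 20% for Intervention 1 against Intervention 2. The control arm has a single setting in 4 × 9 = 36 of 90 allocations (40%).

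**Step 5: with stratification.** If the arms are permuted within each setting, only the 3! × 3! = 36 balanced allocations can occur, and every arm has both settings with certainty.

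**Labels.** The two statements, side by side:

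| Place in Recruitment and Randomisation Procedures | Selangor | Perak |
|---|---|---|
| Opening sentence | rural | urban |
| Paragraph on participants | urban | rural |

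Both cannot be right. The counts above do not depend on which is, because both give three schools per setting.

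**The case against.** The strongest reply is that the article never calls the allocation simple or unrestricted. Random allocation with two schools per arm is also a true description of a stratified scheme, and the sentence that begins "The random selection and allocation of the six schools from the urban and rural locations" may have been meant to convey one. The selection sentence is visibly shorthand: it omits the three-per-area restriction that is stated later. The allocation sentence may omit a restriction in the same way, and an article condenses a fuller protocol. This stands as far as intent goes: the documents do not show that the allocation is unstratified. It does not remove the point, because the procedure is described in some detail and, as described, does not secure the aim set out in Sample Size Estimation.

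Three stronger readings are tempting and are not supported:

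- **That selection is also left to chance.** Drawing six schools from the frame without strata would give three of each with probability C(8,3) × C(7,3)/C(15,6) = 56 × 35/5005 = 1960/5005, about 39%. The article fixes three schools from each area, so this figure does not apply.
- **That setting is fully confounded with arm throughout.** In every unbalanced allocation one arm still has both settings. Complete confounding is limited to the contrast between the two single-setting arms; contrasts with the mixed arm are confounded in part.
- **That inference is invalidated.** Planned Analysis rules out formal comparison and significance testing. The two progression criteria in Discussion and Conclusion, more than 50% of items in the GREEN category and 80% recruitment, are not between-arm contrasts.

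It is also fair to say that the schools already carry an urban/rural classification based on Department of Statistics Malaysia criteria, so the label reversal need not have affected who was placed in which stratum. It is a contradiction to reconcile and carries no weight in the 40% result.

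**Conclusion.** The point holds in conditional form. The allocation is described with no stated restriction by setting, while the design aims to test each condition in both. If it is carried out as literally described, that aim is met in 40% of allocations and missed in 60%, and any given pair of arms is split urban against rural in 20%. These figures assume three urban and three rural schools and equal probability for all 90 allocations. If stratification was intended, the design is sound on this point and only the text falls short.

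The consequence is confined to the descriptive effect sizes, the choice between Interventions 1 and 2, and the ability to report feasibility of each condition in each setting. The contradiction between the Selangor and Perak labels is certain and does not depend on how allocation was done.

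**What to change.** In Recruitment and Randomisation Procedures, state that three urban and three rural schools are drawn at random within stratum, and that within each stratum the three schools are randomly permuted to Intervention 1, Intervention 2 and control, so that each arm has exactly one of each. The urban/rural codes are already held in the 15-school frame and can be passed to the statistician under coded identifiers, which keeps the blinding to school identity.

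Reconcile the two statements on Selangor and Perak. If allocation has already been done, report how it was restricted, if at all, and the urban/rural composition of each arm.

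The cost is a sentence or two and one corrected label, with no extra schools, staff or visits. The change has a limit that should be stated too: with one school per setting in each arm, school and setting remain inseparable within an arm, so arm contrasts stay descriptive even after the fix.

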### Intervention Development

The intervention was developed based on data obtained from systematic reviews (21, 49), reports of the MyHeARTs cohort study (48), and a related qualitative study (50). The findings suggested that a school canteen intervention had merit. The qualitative study was also useful to operationalise the intervention content (50). Focus group discussions with selected adolescents aged 15 years were conducted to understand the available canteen food. The key informants were school headmasters and canteen operators who were interviewed on the dietary habits of students to develop a priority list for intervention (50). All transcripts were analysed and coded. The themes on healthy eating suggestions were availability of healthy options, subsidising healthy foods, and health education and training (50). Stakeholders thought that adolescents' misperceptions, affordability, unhealthy food preferences, and limited availability of healthy options were important barriers preventing healthy eating at school. Furthermore, affordability was a major problem for adolescents in rural schools. Stakeholders perceived that a future school-based intervention might improve the availability and subsidies for healthy foods (50). The intervention was developed and its components guided by the Theoretical Domains Framework for use in behaviour change (51). The research team then mapped potential behaviour change techniques (implementation strategies) to the identified barriers, which will be refined based on considerations of feasibility, potential impacts and context. As a result, two implementation strategies formed the intervention.

### Intervention Overview

This study will explore the feasibility of conducting a dietary intervention in different types of schools (urban or rural) and its potential (evidence of promise) for improving healthy eating practices in adolescents from different socioeconomic backgrounds. It will focus on offering healthy food and beverage options in the school canteen and convenience shop. School canteens will be supposed to support healthy eating based on the healthy canteen guidelines designed by the Ministry of Education (MOE) (52). This will be achieved by increasing the availability and promotion of an extensive range of foods that should make up the majority of a healthy diet (GREEN). AMBER foods can be consumed only sometimes, choosing healthier alternative foods and avoiding large serving sizes that should be eaten in moderation. RED foods are “stop and think foods” that do not meet specified minimum nutrient criteria (RED). The intervention will try to overcome barriers to healthy canteen guidelines implementation and adherence. Specifically, the intervention will assist schools to remove “red-flagged” and “ban” food items from the canteen menu while increasing the availability of “GREEN” menu items. The objective will be to ensure more than 50% of all canteen menu items are in the “GREEN” category. Examples of “GREEN”, “AMBER,” and “RED” food items are indicated in Table 1.

**Table 1 T1:** Food classification description.

	**Everyday foods– “GREEN”**	**Select carefully– “AMBER”**	**Occasional foods– “RED”**
Nutritional quality	• High in nutrients and fibre. • Low in saturated fat and/or added sugar and/or salt.	• Moderate in added fat and/or sugar. • Contribute to excessive kilojoules if consumed in large serving size.	• Very low in nutritional value. • High in saturated fat and/or added sugar and/or added salt.
Foods	• Breads and breakfast cereals (those high in fibre and low in saturated fat and sugars). • Fruits and vegetables. • Reduced-fat dairy products. • Lean meat, fish and poultry. • Eggs, nuts, and legumes. • Commercial vegetable-based soups.	• Full fat dairy products. • Processed meats (e.g., corned beef, chicken loaf). • Commercially produced hot foods (e.g., fried rice, pasta, lasagna, and soup dishes). • Reduced-fat/salt commercially produced pastry based or crumbed hot foods (e.g., meat pies and sausage rolls). • English muffin or pita bread-based pizza. • Margarines, oils, spreads sauces, gravies, dressing and mayonnaise. • Snack food bars. • Un-iced and/or reduced-fat and/or fruit-based cakes, muffins, sweet biscuits, slices. • Savoury snacks foods and biscuits. • Low/reduced-fat ice cream and dairy desserts. • Ice blocks/slushies made with 100% juice. • Breakfast cereals (those refined with added sugar). • Savoury commercial products, snack food bars and biscuits.	• Pastry based or crumbed hot foods (e.g., meat pies, sausage rolls). • Processed meat such as salami (unless reduced-fat/low salt). • Fried foods. • Commercial pizza products. • Savoury snack foods–crisps, chips, biscuits or similar products. • Ice-creams and dairy desserts. • Iced cakes, muffins, sweet biscuits, slices. • Cream, butter and chocolate-based spreads.
Drinks	Water. 99% fruit juice in 200 mL serves or less.	99% fruit juice in serves >200 mL but <300 mL.Artificially sweetened drinks.	All sugar-sweetened drinks with >300 kJ per serving and/or >100 mg of sodium per serve are banned from sale in school canteens.

### Intervention Components and Implementation

#### Intervention (1) (Training Only)

Training: canteen and school convenience shop operators will be requested to provide healthy foods and drinks and consider alternative methods of cooking by using a training manual (canteen and school convenience shop operators), which will be developed based on the Malaysian Healthy Canteen Guidelines (52). Canteen managers and staff will be invited to attend a 1-h training workshop to educate them on healthy eating policy, nutrition, canteen stock, and change management. They will also be provided with a “Healthy Canteen Booklet” and will be trained in choosing healthy cooking methods, such as steaming and grilling.

#### Intervention (2) (Training + Subsidy)

The intervention will intend to increase the (i) intake of fruits and vegetables and (ii) consumption of healthy and lower energy *kuihs* (e.g., *keladi rebus (steamed yam), apam (pancake)*, and non-sweetened beverages (e.g., water), rather than high energy-dense snacks and drinks (measured by their sales receipts, dietary intake, coupons).

➢ Training: Canteen and school convenience shop operators will have to provide healthy food options and consider alternative methods of cooking by using the Training Manual developed based on the Malaysian Healthy Canteen Guideline (52). A trained dietitian who is the main investigator of this study (HM) will deliver the training in these two schools, and the canteens will be assessed each week on the foods they sell.➢ Fruits, vegetables, and low energy-dense (low ED) *kuih* (traditional cakes) will be subsidised. The canteen operators in this group of interventions will receive a weekly allowance (the amount will be modified when necessary) to sell fruit, vegetables, and low ED *kuih* (e.g., *Ketayap, Cakoi, Cucur cempedak, Apam*) at subsidised prices.➢ All students (Form three students) will receive (Ringgit Malaysia RM 2) coupons that subsidise the price of fruits (will provide 2 days weekly over 4 weeks) and low ED *kuih* (given 2 days weekly over 4 weeks). Therefore, the total value of coupons per week for one student will be RM 4. This coupon will be given to the students weekly. When they buy fruit/*kuih*, the coupon will be placed in a specific box, and the teacher in charge will collect them daily and keep a record of how many coupons have been used as the subsidy.➢ In the subsidised group, schools will be provided with funds to prepare healthy food. This will give them additional money for their weekly purchases to prepare extra vegetables for the study participants. For example, if they purchase vegetables worth 200 Ringgit (RM) per week, they will get 100 Ringgit (RM) subsidy so that they can prepare an extra tray of vegetables per week. The dietitian will visit the school on a weekly basis for evaluation. The receipts of the vegetables will be given to the dietitian, who will monitor them by visiting the school every week to examine the report by the teacher in charge.➢ Providing free drinking water by installing a proper water container/tank to dispense drinking water. The dietitian will check every week whether the water will be filled up during the school period and whether it will be utilised by the students. This will be recorded by the teacher in charge and cross-checked during the weekly visit of the dietitian.

#### Control

The control group will consume the food are typically available at the school canteen and convenience shop. No intervention will be made in terms of their food choices as well as no advice nor resources will be provided during this intervention period. The canteen and convenience shop operators will have their usual service without changes at two schools, which will be considered as the controls. The control school will receive usual healthy canteen guidelines as given by the Ministry of Health.

### Data Collection

Data will be collected at baseline and post-intervention. All six eligible governmental schools with an operational canteen will be required to complete baseline data collection. The schools' characteristics, including school size, location, and the number of days the canteen operates, will be captured before randomisation. Furthermore, canteen vendors will be asked to show the serving menu that captures all foods (even snacks and beverages) available for sale at school canteens to the research team before the canteen checklist assessment.

### Dietary Assessment

A questionnaire will be used to obtain information regarding adolescents' dietary intake. This study will use a validated 3-day diet history to ensure greater accuracy, namely to estimate the respondents' energy intake (16). The tool was pre-tested on 40 participants from two different schools (one school each from rural and urban areas, respectively) (16). Qualified and trained dietitians will conduct an open-ended interview with adolescents to collect information on their food habits through the day (breakfast, mid-morning snacks, lunch, afternoon tea, dinner, and supper). A flip chart will be used as an additional tool to assess the subjects' diet and help estimate their portion size. Nutritionist Pro™ Diet Analysis software will be used to assess the nutritional content of the food (16).

Any misreporting may be heightened in dietary intervention studies. A reliable and valid short form of the Marlowe-Crowne social desirability scale will be administered to identify and control participants prone to these traits (53).

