## Methods

### Overview of Study Methodology

This study is part of the MyHeARTBEaT project (IF017-2017) approved by Research Ethics Committee at the University of Malaya Medical Centre (MREC ID NO: 2018214-6029). The study was registered at the ISRCTN registry: ISRCTN 89649533. The trial design is a three-arm, parallel-group, un-blinded, feasibility cluster randomized controlled study undertaken within six schools in Selangor and Perak states in Malaysia. It will compare two intervention arms (1 and 2) against a usual practice control conducted in six secondary schools, of which four schools will receive the interventions and two will serve as controls. Two interventions are proposed which will focus on providing healthier food options available for sale at the school canteen and convenience shops in the selected schools. Intervention 1 will entail training the canteen and school convenience shop operators to prepare healthier food options in the canteen. The research team will train food operators on the benefits of selling healthy food. Intervention 2 also will create awareness, with the cooperation of food vendor operators among students on consuming healthy food. It will include subsidising the price of vegetables, fruits, and low energy-dense *kuih* (traditional cake). The training of the canteen and school convenience shop operators will follow intervention (1) and focus on training the staff who will sell subsidised fruits, vegetables, and low-energy *kuih*. The control group will continue to sell the usual food.

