### Outcomes

#### Potential Trial Outcomes

As this is a feasibility study, the focus of the current study will be whether the intervention can be delivered as intended and desired outcomes can be attributed. It is envisaged that if we have to move to a larger trial that the primary outcome will be the participants' consumption of healthy canteen items. The participants will be deemed as consuming healthy canteen items or green foods based on their dietary intake of more than 50% of listed menu items. The canteen operators will be tasked with auditing the green items available for sale at the school canteen. During follow-up, two dietitians will audit the results based on the canteen audit and discussion with canteen staff. Food classification tools and guidelines published by the Ministry of Education in Malaysia will be used to categorise the food (see Table 1).

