### Participant Confidentiality

All study personnel will be trained in the requirements to ensure the participants' confidentiality. The principal investigator will protect the confidentiality of participants' information. Participant identification code will be assigned upon study enrolment. The data will be kept centrally by the principal investigator and will be anonymised and identified by a unique code. Moreover, access to personally identifiable information will be limited to members of the research team. Documents that will not be anonymised, such as signed informed consent forms will be held by the principal investigator in a locked cabinet in the department at the university.

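### The trial is declared un-blinded and describes no masking of the diet interviews or of the classing of diet records, so assessor judgement can enter the descriptive effect sizes

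*Protocol article*

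**What the plan says.** All references are to the protocol article.

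- **Design.** Overview of Study Methodology describes a "three-arm, parallel-group, un-blinded, feasibility cluster randomized controlled study". The only person described as masked appears under Recruitment and Randomisation Procedures: selection and allocation are done by "an independent statistician from the University of Bristol who will be blind to the school identity".
- **Collecting diet data.** Dietary Assessment states: "Qualified and trained dietitians will conduct an open-ended interview with adolescents to collect information on their food habits through the day". The tool is a 3-day diet history, with a flip chart to help estimate portions. For nutrients, "Nutritionist Pro™ Diet Analysis software will be used to assess the nutritional content of the food". The section acknowledges that misreporting may be worse in dietary intervention studies and answers with one safeguard: a "short form of the Marlowe-Crowne social desirability scale will be administered to identify and control participants prone to these traits".
- **Classing.** Potential Trial Outcomes states: "Food classification tools and guidelines published by the Ministry of Education in Malaysia will be used to categorise the food". It names consumption of healthy canteen items as the primary outcome envisaged for a larger trial, with a threshold of more than 50% of menu items.
- **Records.** Participant Confidentiality states that the data "will be anonymised and identified by a unique code". Members of the research team keep access to identifying information.
- **Use of the results.** Planned Analysis rules out formal comparison of the arms, significance tests and p-values, but keeps effect sizes as the basis for judging effects. Discussion and Conclusion makes progression depend on the GREEN share of menu items (above 50%) and on recruiting 80% of eligible participants.

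**The concern.** Students and canteen operators cannot be masked to training, coupons and subsidised prices. The person who later turns a diet record into food classes largely can be, yet the article applies the un-blinded label to the whole study and makes no exception for outcome assessment. An open-ended interview, portion estimation and food classing each call for judgement. The social desirability scale deals with what the student chooses to report. It does nothing about how the dietitian probes or how a coder resolves a doubtful item.

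Two things are at stake. The first is the effect sizes on diet, which this study will report and which may colour planning of the full trial: a tilt in probing or classing that depends on the arm would look the same as evidence of promise. The second is the measurement procedure itself. One stated aim is to test whether changes in food choices can feasibly be assessed. If masked coding is not tried here, the study cannot show that it works before it is needed.

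**Working it through.** The documents give no inter-rater figure, misclassification rate or standard deviation, so there is no calculation to reproduce. The check is to set the sections side by side.

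1. **Who is masked?** Only the statistician who selects and allocates schools. That person assesses no outcome.

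2. **Who interviews?** Dietitians described as qualified and trained. The section does not say whether they are the same people as those with other roles.

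3. **Which dietitian roles know the arm?** Under Intervention (2), the main investigator is a dietitian who delivers the training in those two schools. Under External and Internal Audit, two external dietitians are assigned to the intervention schools over the four weeks. Both roles know the arm. The article neither states nor excludes an overlap with the diet interviewers.

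4. **Who classes students' records?** Not stated. The staff named under Potential Trial Outcomes (canteen operators, then two dietitians) audit menu items, which is a different task.

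5. **Does the classification remove discretion?** Not on the evidence of Table 1:
   - Savoury snack foods and biscuits appear under both AMBER and RED.
   - Fried rice is AMBER, while fried foods in general are RED.
   - Commercial vegetable-based soups are GREEN, while soup dishes are AMBER.
   - Kuih has no entry, although low energy-dense kuih is subsidised in Intervention 2.

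   The first two overlaps lie between AMBER and RED and would not change a GREEN count. The soups and the missing kuih entry do bear on what counts as GREEN. Because the outcome is a threshold, a few doubtful items can move a student near it from one side to the other.

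6. **Would such a tilt average out?** There are two schools per arm, each expected to supply 75 to 80 students, so an arm has 2 × 75 = 150 to 2 × 80 = 160 students and one school supplies half of them. A habit of probing or coding tied to one school would affect half of that arm's data.

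7. **Does the participant code already mask?** Not by itself. It is a confidentiality measure, and the research team keeps access to identities. It does give masked coding a starting point, since only school, arm and time point need to be stripped as well.

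8. **Where could the bias go?** Into the descriptive effect sizes on diet. The progression rule uses menu share and recruitment, so bias in the student diet data does not reach it.

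**The case against.** The strongest reply is that the article states nothing false. It openly declares an un-blinded feasibility design, plans no test between arms, and may have left the coding procedure to a full protocol that is not shown. Published Ministry tools narrow the coder's freedom. Masked coding also cannot repair bias that arose in the interview, where portions appear to be estimated. An interviewer on site can learn the arm, and coupon fruit or subsidised kuih in a record may reveal it to a coder.

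Most of this stands and limits the point. It does not dispose of it: the unqualified un-blinded label is a stated choice, effect sizes will still be judged, and Table 1 shows that some discretion remains.

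Several stronger readings are tempting but unsupported:

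- **That staff who know the arm class the diet records.** This is an inference from the un-blinded label. The article does not say who classes them.
- **That the same dietitians train, audit and interview.** This is argued from silence.
- **That the bias would decide progression or the choice of intervention.** The progression rule omits student diet, and the choice between Interventions 1 and 2 is tied only to the feasibility findings in general.
- **That the bias can be sized.** If 5%, 10% or 20% of items were discretionary and all were resolved to GREEN in intervention schools only, the mean GREEN share would shift by up to 5, 10 or 20 points. Those rates have no source in the document, the result merely restates the assumption, and the stated outcome is a threshold rather than a mean share.
- **That masking would cost nothing.** It needs file preparation and some scheduling.

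**Conclusion.** The point holds in a limited form. The article describes no masking of diet interviewing or of the classing of students' records, for an outcome that involves judgement and is envisaged as primary in the later trial. The risk is confined to the descriptive effect sizes on diet and to what this study can establish about the measurement procedure. Its size cannot be computed from the document. No sample size, error rate or progression criterion changes.

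The conclusion assumes that the un-blinded label means what it says for outcome assessment. If a full protocol already provides for masked coding, the remedy reduces to saying so in the design description.

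**What to change.** In Dietary Assessment and Potential Trial Outcomes, state that:

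- existing staff enter and class diet records from files showing only the participant code, with school, arm and time point removed;
- diet interviews follow a scripted probe list;
- where the existing roster allows, a dietitian who trained or audited at a school does not interview its students.

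In Overview of Study Methodology, describe the trial as un-blinded for delivery and masked for diet coding.

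The cost is some wording, a file-stripping step and minor scheduling work, using staff and codes already in place. The article should also state the limit: these steps reduce assessor bias but do not remove it, because interviewers may learn the arm at the school and subsidised foods in a record may disclose it.
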